### Recruitment of schools and participants

All (sub)urban schools following a regular education program were eligible for participation ranging from primary school level, and lower vocational training to secondary school. All schools located near the Nijmegen area were invited to participate in the *MyMovez* project. Further, Dutch Public Health Services (GGD) of each province were contacted to promote the *MyMovez* project at their regions. In addition, schools were invited to participate via personal contacts of students and researchers. This random procedure resulted in the participation of 21 (sub)urban schools throughout the Netherlands for Phase I of the *MyMovez* project. See Fig. 1 for a flow diagram of the recruitment procedure.

**Fig. 1 Fig1:**
[figure not shown]
Flow diagram of the MyMovez recruitment procedure

After obtaining (written) consent of the school’s principals, parents/legal guardians received an information letter and/or e-mail via the school announcing the project’s goals, planning, execution and safety procedures. Parents/legal guardians could enlist their child to the *MyMovez* study by giving consent on either a paper-and-pencil or digital form on the *MyMovez* website (www.mymovez.nl). The *MyMovez* website provides easily accessible information and updates about the project, team and progress (e.g., by a video illustrating how a day looks like for a participant, Q&A page, photos, and infographics). Researchers also visited schools to explain and promote the project in school classes and to hold information meetings for teachers, student mentors, and parent advisory boards.

Despite the schools’ and researchers’ efforts to promote the *MyMovez* project, parents/legal guardians did not always take notice of the research (e.g., the response rate at some schools was < 5%), resulting in disappointed pupils who wanted to participate on the day the research materials were handed out to their classmates. These pupils were given the opportunity to contact their parents/legal guardians to give their consent via the website or hand in a written consent form after the school break. In addition, pupils had the opportunity to participate during each of the following data collection waves, which has thus far resulted in different sample sizes for each data wave (in combination with drop out cases): *n* = 792 in Wave 1; *n* = 852 in Wave 2; *n* = 824 in Wave 3 and *n* = 671 in Wave 4. It is expected that the participation rates for Wave 5 (February 2018) will differ as well due to attrition and new participations.

### Wearable lab

In this comprehensive project, the innovative research tool *Wearable Lab* is developed to collect a unique longitudinal dataset according to the highest standards in ethical and legal safety regulations. The smartphone with the *MyMovez* research app is connected to an activity tracker that both generate different types of data that are transferred wirelessly to a secured data server. Data types are self-reported and peer-reported (i.e., short surveys and sociometric queries, respectively) and experience sampling data, *Social Network Beacon* data, real-time physical activity data (i.e., steps and cycling) and location information, photos and chat conversation data on individual and class level by the social media platform *Social Buzz* (added to the *MyMovez* research app since January 2017). These data are used to examine youth’s media and social network exposure, socialization experiences, psychosocial determinants of behavior, and energy balance-related behaviors.

Social network information is gathered by asking youth to nominate peers with various characteristics (i.e., who is a leader?) as well as by recording chat connections and reports between participants on the social media feature *Social Buzz* in the *MyMovez* research app. In addition, social network information is also collected using the *Social Beacon Network*, in which the smartphones detect and register the research phones of interaction partners during multiple time points a day via Bluetooth. These data collection methods collectively provide insights into micro-processes (with multiple measurement points during a day) as well as macro-processes (multiple assessments across a school year). Furthermore, these methods provide information about youths’ perceived networks (i.e., sociometric items) as well as more objective assessments of networks based on physical proximity (i.e., the *Social Beacon Network)*.

Furthermore, the *Wearable Lab* allows for the collection of other novel types of data such as photo queries and global positioning system (GPS) data. For example, photo data are coded and used for machine learning purposes (e.g., coding of food or media use pictures) contributing to the examination of youth’s diets, social media behavior and other daily activities [37]. The GPS data provides information about cycling^1^ (the activity tracker only counts the amount of steps and the intensity) and the physical environment, by linking these to Geographic Information System (GIS) data in which youth are exposed to food and PA related facilities [38]. All together, the *Wearable Lab* allows for the collection of a comprehensive set of data that provides the opportunity to address all of the project’s research goals.

Participants receive surveys, photo questions or notifications on daily randomized or fixed time points. In addition, the researchers can personalize for each school class the time schedule in which participants are allowed to receive questions and notifications (i.e., before and after school and during school breaks only). Regularly used answering categories are already available in the backend of the app which saves researchers time in programming the surveys. In addition, it is possible to include follow-up or feedback loops based on answers to closed questions or PA measured by the activity tracker, send jokes/memes, riddles, and *MyMovez* news flashes. To keep the participants engaged, the app also includes two games (Zoko and Snake; which are allowed to play 5 min./hour) and participants can create and adjust their own avatar (e.g., face characteristics, hairstyle and -color, and additional attributes such as animals, music instruments, fruits, or sport gear). Participants also have the opportunity to chat with their classmates or with a researcher to ask research related questions, report misconduct, or ask for help.

### Procedure

Most schools were visited in advance to promote the research project among the participants before the project started. On the starting day of the initial data collection, trained researchers handed out the research materials (i.e., smartphone and activity-tracking bracelet) and instructed the participants in class or in small groups of approximately 5-8 school children about the use of the *Wearable Lab*. Specifically, it was explained how to turn the phone on and off, how to use the social chat and avatar, how to check whether the activity tracker is connected to the smartphone, how to check whether the batteries are full, and what to do when the phone displays an error. Participants were also told that they should wear the activity bracelet for the entire week and that the activity bracelet is water resistant. Participants were also shown a short movie clip about how a research day with the *Wearable Lab* looked like and they were handed a code of conduct showing how to behave in the *Social Buzz* social media platform. Next, participants signed an assent form and an additional agreement in which they promised to handle the research equipment with care during the 7-day period they were borrowing the research materials. Participants were informed that they could withdraw from the research at any moment, and that their data can be deleted if they or their parents want to. After the instructions they were provided with the opportunity to ask questions and could return to their classrooms. Each year (during Wave 2, 4, and 5), participants’ weight and height is measured individually in a separate room by a trained researcher. Depending on the school schedule, this is done after the instruction or participants are called a second time from their classroom.

On the starting day of each measurement period, participants receive questions after their school day ended. During the following days, they all receive questionnaires at random time points during the day, but never during school hours or at night between 7:30 PM and 7:00 AM. At the end of the measurement period, reminders are sent to the participants when and where they need to hand in the research materials at their schools. Researchers collect the research materials at the schools.

### Measurements

Data collection involves explicit self- and peer-reported survey measures (short digital questionnaires administered via the smartphones), objective measures (photos, real-time data, activity tracking, cycling, *Social Beacon Network* and *Social Buzz* data), and researcher-assessed measures (participants’ height and weight). Most survey measurements used in the *MyMovez* project are existing validated questionnaires, translated into Dutch. Some (parts of) questionnaires are adapted from validated questionnaires and tailored to identify specific behaviors. In cases in which no validated measures are available, new items or scales are developed for the *MyMovez* project. All measurements used in the *MyMovez* project described in the following paragraphs. The survey instruments are listed in Table 1 and described into detail in Additional file 1.

**Table 1 Tab1:** Overview of survey measures MyMovez project – Phase I

	Content/captures	Instrument(s)	Reference(s)
Individual measures			
	Self-esteem	Rosenberg Self-esteem scale	[49]
	Body esteem	Figure Rating Scale	[50, 51]
	Need to belong	Need to belong Scale	[52]
	Fear of Negative Evaluation	Brief Fear of Negative Evaluation Scale	[53]
	Happiness	The Faces Scale	[54]
	Pro-social behavior	Strengths and Difficulties Questionnaire	[55]
	Public individuation	Public individuation	[56]
	Self-profiling of personality characteristics	Descriptive	[57]
Behavioral and motivational constructs of energy intake and expenditure			
	Theory of Planned Behavior (attitude, self-efficacy, descriptive and injunctive norms, and intentions)	Theory of Planned Behavior constructs	[26, 58, 59]
	Motivation	Adapted measures from the Health Care SDT Packet Perceived competence scale	[60]
	Fogg Behavior Model (determinants motivation and ability with antecedents pleasure/pain, hope/fear, and social acceptance/rejection, time, money, physical effort, brain cycles, social deviance, and non-routine)	- Fogg Behavior Model - Theory of Planned Behavior constructs - Adapted measures from the Physical Activity Enjoyment Scale PACES - Adapted measures from the Perceived Benefits of Physical Activity Scale - Adapted measures from the Self-Report-Habit-index Scale (SRHI)	[29] [58, 59] [61] [62] [63]
	Opinion Leadership	- King and Summers Opinion Leadership scale - Opinion Leadership scale	[23] [24]
	Perceived social support	Social support scale	[64]
Energy intake related measures			
	Consumption behavior (hunger, thirst, including specific Dutch snack and drink items)	- Food Frequency Questionnaire (FFQ) based on the Dutch EPIC Frequency Questionnaire	[65] [12]
	Role models or ‘prototypes’ of consumption behavior	Prototype-Willingness Model	[66]
	Self-regulatory resources (internal and external attribution)	Nutrition Locus of Control	[67]
	Dieting behavior	Descriptive	
	Physical environment diet (availability and accessibility)	- Questionnaire to assess determinants related to fruit and vegetable intakes in children - Child-reported family and peer influences questionnaire	[68, 69]
	Parental role modeling	adapted from the Home Environment Scale	[70]
	Occurrence unhealthy eating behaviors	Descriptive / filler items	
Energy expenditure related measures			
	Athletic competence	Perceived Competence Scale for Children	[71, 72]
	Barriers to Physical Activity (body-related, resources, social, fitness, and inconvenience barriers)	Barriers to PA scale	[73]
	Daily activities and sports participation (which sports they play and like)	Descriptive / filler items	
	Environmental factors	Descriptive	[74]
	Habitual physical activity	- Activity Questionnaire for Adolescents and Adults - Questionnaire to Assess Health-enhancing physical activity - ‘Day in the life’ Questionnaire	[75] [76–78] [79]
	Social norms and perceived physical activity	Adapted from TPB constructs	[58, 59]
	Injury check	Descriptive	
	Motives for being physically active	The Self-presentation Motives for Physical Activity Questionnaire	[33]
(Social) Media consumption			
	Television (TV) exposure (duration of exposure, type of TV stations, genre TV programs)	Descriptive	[80] [81]
	Internet and social media exposure (duration of exposure, type of social media platforms)	Descriptive	[80] [81]
	Video blog (Vlog) exposure (duration of exposure, names of Vloggers, type of Vlogs)	Descriptive	
	Gaming behavior (duration, type and genre of games, which devices used, most liked)	Descriptive	
	House rules on media use (screen-based activities)	Activity Support Scale for Multiple Groups	[82]
	Mealtime media use	Descriptive / filler items	[83]
	Use of health apps and Wearables (most liked, app effectiveness)	Descriptive / filler items	
Research and app evaluation			
	Evaluation research and app (liking en enjoyment research and app, games, avatar, jokes and memes, and *Social Buzz*)	Descriptive / filler items	
Filler items			
	Naming favorite foods, music, brands, animals, movies, celebrities, sports and sports heroes, daily planning, etc.	Descriptive / filler items	

Outcome variables (e.g., social network characteristics, physical activity, drink and snack consumption), as well as TPB and motivational measures, are measured at each data wave assessment. Other measures are divided over the different data waves. A detailed scheme can be provided upon request to the corresponding author. Participants’ name, birth date, gender and postal code were provided by the school^2^ to create an ID number in the back-end of the *MyMovez* research application.

#### I. Survey measures

##### Demographics

Self-reported demographics are assessed in a survey during the start of the project (and for every new participant that enrolled in later waves), consisting of participant’s age, sex, grade level, nationality, caregivers’ nationalities, and whether they have older and younger, male or female siblings.

##### Body mass index (BMI)

Participants’ weight and height are measured individually by a trained research assistant according to standard procedures (without shoes but fully clothed) in wave 2, 4, and 5. Height is measured to the nearest 0.1 cm using a stadiometer and weight to the nearest 0.1 kg using a digital scale. Participant’s Body Mass Index (BMI) is calculated using the standard formula weight [kg]/height2 [m]. The BMI-scores are standardized by using the LMS-method, which accounts for variations in growth curves of children and adolescents of different ages and gender for different countries. BMI (z-score) cutoff points were used representing the current z-BMI standards for Dutch children and adolescents [39]. Self-reported measures about height en weight are assessed when participants entered the project after Wave 2 (when weight and height were measured by the researchers).

##### Socioeconomic status

The socioeconomic status of the participant’s family is measured with the second version of the Family Affluence Scale (FAS II) [40]. This scale consists of six items concerning the number of computers, laptops or tablets, cars and bathrooms in the household, and a question about the number of holidays the family could afford each year. In addition, it is asked whether the participants have their own bedroom, and whether there is a dishwasher in the household. Answering categories about the bedroom and dishwasher are dichotomous. Other answering categories ranged from ‘*None*’ (0) to either ‘*Two or more*’ (2) or ‘*Three or more*’ (3). The sum score of the scale (ranging between 0 and 13) indicates a higher socioeconomic status. In addition, the participant’s postal codes provide information about their socioeconomic status. The neighborhoods in which participants live are classified on socioeconomic status by Statistics Netherlands.

#### II. Sociometry and social beacon network

##### Sociometric questions

To map social network structures and identify social influence agents for the health behaviors, participants are asked to complete a total of 16 peer nomination items during the course of the research week (approximately 3 questions per day). The class name list provided by the schools are uploaded into the backend of the *MyMovez* app, so participants can scroll down the list and tick off names of peers who are in the same grade regardless of their participation in the *MyMovez* project.^3^ Participants could nominate an unlimited number of peers for each item, but could not nominate themselves. Participants are required to nominate at least one peer for each item.

The general network questions are based on previous research [9, 12, 19]: ‘*Who are your friends?*’, ‘*Who do you ask for advice? With this we mean children from you class or school whose opinion you value.*’, ‘*Who are leaders or take the position of leader in a group?*’, ‘*Who do you respect? With this we mean children you admire, because they, for example, are good at something.*’, ‘*With whom do you spend time?*’ In addition, questions are added to detect innovators (‘*Who often has new gadgets and clothes?*’) and ask about modeling behavior (‘*Whom do others want to look like?*’).

Additionally, participants are asked to nominate peers for each of the specific health behaviors (dietary intake, physical activity, and media use) to detect innovators, role models, impression managers, and messengers. For example, ‘*With whom do you talk about what you eat or drink?*’ (dietary communication), ‘*Of whom do you think it is important that they see you as someone who is physically active?*’ (PA impression management), and ‘*Who eats or drinks products that you would like to eat or drink?*’ (dietary modeling).

In addition to the sociometric questions, participants are also asked from which source they like to receive advice about eating healthy snacks, physical activity and media use, and would follow advice from, with several reference groups as response options (e.g., peers, older adolescents, celebrities, vloggers, parents, experts, teachers).

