##### Social beacon network

Social networks are also assessed with Bluetooth technology to detect proximal peers via smartphones. The *Social Beacon Network* is an innovative unobtrusive way to measure physical distances between all participants. The research smartphones scan and detect other participants’ phones that are within Bluetooth range (approximately 10 m). When participants are within close proximity for more than half an hour, two questions are triggered to check whether participants are actually spending time together and to avoid measurement error caused by participants passing by accidentally while the phone was scanning the proximity (‘*Are you spending time with someone?*’ If so, ‘*With whom are you spending time?’*). In addition, they are asked to indicate what they are doing in an open-ended format. The Social Beacon Network provides one way of validating the sociometric questions and the social networks created from these items.

In conclusion, the *Social Beacon Network* can provide insights into the relative frequency of interactions between individuals (with multiple measurement points) during the day, which complement the sociometric items, which are only assessed once per data collection wave. This unobtrusive research method requires new data management strategies that are being developed during this project.

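### On items about a pupil's own ties, the one-peer minimum leaves no way to record a truthful 'nobody', so some recorded ties are forced, by an unknown amount

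*Protocol article*

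**What the plan says.** Under Sociometric questions, pupils answer 16 nomination items once per wave by going through a school-supplied list, on which they "tick off names of peers who are in the same grade regardless of their participation in the" project. There is no upper limit and no self-nomination: "Participants could nominate an unlimited number of peers for each item, but could not nominate themselves". The next sentence sets the floor: "Participants are required to nominate at least one peer for each item". No exception, skip or 'nobody' answer is described.

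The rule covers items about the pupil's own contacts and wishes. Examples are advice ("Who do you ask for advice? With this we mean children from you class or school whose opinion you value"), dietary communication ("With whom do you talk about what you eat or drink") and dietary modeling ("Who eats or drinks products that you would like to eat or drink"). It also covers items on which the pupil judges others, such as who leads or who has new gadgets.

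The Social beacon network section works differently. It first asks "Are you spending time with someone" and requests a name only after a yes. The stated reason is to avoid measurement error.

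Part A of the Background says influence agents will be studied by comparing traditional with behavior-specific nominations across several centrality measures. Strategy of analysis names indegree, KeyPlayer searches, dyadic models and stochastic actor-oriented models.

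**The concern.** On the own-tie items, 'nobody on this list' can be the true answer. The article gives grounds for this. The advice item refers to class or school while the list holds the same grade, so a pupil whose only adviser is in another grade has no correct name to tick. The article also asks separately which sources pupils want health advice from, and offers parents, teachers, vloggers and experts as well as peers.

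Under the floor, such a pupil either ticks a name that is not a true tie or does not answer. The first adds a false tie; the second is a missing value. Neither is a recorded zero, and no later analysis can recover the lost answer from the item alone.

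At stake is one of Part A's own questions: whether general or health-specific nominations better identify influence agents. If true zeros are more frequent on some items than on others, the networks being compared carry different amounts of forced content.

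**Working it through.** The article gives no figure for this point, so there is none to reproduce. The check has a logical part and an illustration.

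**Logic.** A completed item has at least one outgoing tie. A true outdegree of zero therefore cannot be recorded on a completed item. The floor acts on ties sent; a pupil whom nobody names can still have indegree zero.

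**Inputs.**
- Floor of 1 per item (Sociometric questions).
- Class size n = 25 (Design), used only for illustration.
- q, the share of pupils with no true tie on the item: not in the documents; assumed 5% to 30%.
- m, the mean number of names among the other pupils: not in the documents; assumed 2 to 5.
- Each forced pupil gives exactly one name, and all pupils answer.

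**Forced ties per class and item** = q × n: 0.05 × 25 = 1.25 up to 0.30 × 25 = 7.5. The lowest density that can be recorded is 1/(n − 1) = 1/24 = 0.042.

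**Forced share of recorded ties** = q / (q + (1 − q) × m). For example, q = 20% and m = 3 gives 0.20 / (0.20 + 0.80 × 3) = 0.20 / 2.60 = 7.7%.

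| q | m = 2 | m = 3 | m = 5 |
|---|---|---|---|
| 5% | 2.6% | 1.7% | 1.0% |
| 10% | 5.3% | 3.6% | 2.2% |
| 20% | 11.1% | 7.7% | 4.8% |
| 30% | 17.6% | 12.5% | 7.9% |

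**Chance that a given pupil receives at least one forced nomination**, if forced names fall at random: 1 − (23/24)^(q × 25), which is 5% at q = 5% and 27% at q = 30%.

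**Comparison between items.** At m = 3, an item with q = 5% has 1.7% forced ties and an item with q = 20% has 7.7%. With equal q and m the shares are equal. The distortion therefore depends on a difference between items that the documents do not report.

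**What deleting every single-name answer would do.** Suppose true nominators give 1 + Poisson(1) names (mean 2). Then e^(−1) = 36.8% of them name exactly one.
- q = 10%: true single names 0.90 × 0.368 = 0.331, forced 0.10. True share of the deleted ties: 0.331 / 0.431 = 77%.
- q = 20%: 0.80 × 0.368 = 0.294, forced 0.20. True share: 0.294 / 0.494 = 60%.

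Under these assumptions, blanket deletion removes mostly true ties.

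**The case against.** The strongest reply is that the size is assumed throughout. Nominations are unlimited, so m may be large, and with few true zeros the forced share is about 1%. This stands; only the mechanism is certain.

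A reader might go further than the documents allow in four ways.
- *All 16 items are corrupted.* Several ask about others (leaders, new gadgets, whom others want to look like), where a pupil's own lack of contacts does not make 'nobody' true. Friends and time spent together are also weak cases. Only ten of the 16 items are worded in the article.
- *Selection and influence effects are attenuated.* Strategy of analysis describes similarity in the stochastic actor-oriented models in terms of friends, and nothing shows that forced answers matter on the friendship item.
- *The wrong influence agents will be chosen.* If forced names fall at random, each pupil's expected indegree rises by about q of a nomination. That is noise without systematic re-ranking. If pupils name the nearest fit, the tie is weak rather than arbitrary.
- *The harm is worst on the health-specific items or at age 8-12.* This is plausible, but nothing in the article documents it.

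Additional file 1 and the text of the footnote on the name list are not shown. Either could qualify the rule, but nothing visible does, and the footnote marker sits on the name-list sentence, not on the minimum. Beacon and chat data give other views of the network, but proximity cannot show that an advice or role-model tie is absent.

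**Conclusion.** The point holds for items about the pupil's own ties. The rule is stated without exception, and following it puts some forced ties into the advice, talk, impression-management and modeling networks. Their share is unknown: about 1% to 18% per item under q = 5% to 30% and m = 2 to 5, with one forced name per affected pupil. The general-versus-specific comparison is distorted only if true zeros differ between items, which the documents neither show nor rule out. This is a measurement weakness to estimate and report. The article does not show that it invalidates the network analyses.

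**What to change.** **Wave 5** (still to come in the article). Keep each nomination item unchanged so that it stays comparable with Waves 1 to 4. For the own-tie items, add a yes/no follow-up after the nomination is stored, asking whether there really is such a person, and store the answer separately from missing. The Wearable lab section says the app supports follow-ups triggered by closed answers, and the beacon question already uses a yes/no step. Replacing the item with a 'nobody' button at Wave 5 alone should be avoided, because ties would then seem to dissolve between Waves 4 and 5 merely through the change of format.

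**Waves 1 to 4.** From the Wave 5 answers, estimate for each item the share of single nominations that were forced. Repeat the centrality analyses and the general-versus-specific comparison with single nominations on these items down-weighted, or removed at random, at that rate. This assumes the Wave 5 rate applies to pupils up to two years younger, which should be stated. Removing all single nominations may be reported as an extreme bound only, and not as a test that conclusions must pass.

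**Phase II.** Offer a direct 'nobody' answer.

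**Cost.** A few extra short questions at Wave 5 and one extra sensitivity analysis.
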